### Harms and benefits

2.7

The medical device used in this study has the ability to measure the range of motion exercises, providing biofeedback through surface EMG measurement and neuromuscular electrical stimulation therapy. Each method is a commonly used treatment method for rehabilitation. The range of motion exercises and biofeedback through surface EMG measurement are not expected to be inconvenient or risky to the user. Neuromuscular electrical stimulation therapy is an electrical stimulation via medical electrodes. Since there are no reports that document any side effects or complications from neuromuscular electrical stimulation therapy, safety is not a major concern.^[26]^ Although there may be subjective discomfort in performing neuromuscular electrical stimulation therapy, the intensity can be controlled by the subject; instructions for controlling the intensity will be adequately explained. If there is a situation that requires termination of the therapy due to discomfort or other medical or subjective reasons, they will be withdrawn from the study immediately and reasons for discontinuation will be recorded.

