**Discussion::**

This study is a prospective, single-center, randomized, controlled study. This study aims to research the feasibility and efficacy of a 6-week, structured home-based rehabilitation program for patients after ACL reconstruction using a smart wearable device. The findings of this study will help to establish a home-based rehabilitation program to better recovery in patients with ACL reconstruction.

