NMES will be performed with an isometric exercise in sitting position with the knee extended. The patient will first contract the quadriceps muscles, and electrical stimulation will begin only when the force exceeds 75% of MVIC. The device delivers biphasic rectangular waveform pulses (pulse duration 400 μs, frequency of impulses 2500 Hz, train of pulses frequency 50 Hz). A total of 15 contractions is sustained for 15 seconds (inclusive of 2 seconds ramp up and down), each with 50 seconds off time. The total time for 1 set of NMES is about 22 minutes. Patients will be recommended to use NMES at least 3 times a day, about 66 minutes per session. The amplitude should be set at an intensity that is high enough to produce a full, sustained contraction of the quadriceps with visual and/or palpable evidence. The initial intensity will be set for each subject when a physical therapist trains and explains the device and exercise. The stimulus intensity will be increased further to maximum subject tolerance. As the rehabilitation program progresses, the intensity of NMES will be changed as the subject's maximal tolerable level (Fig. 3D). Exercise data using the device will automatically be stored on the device and will be used for analysis.

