### Assessment

2.6

The primary and secondary outcomes will be assessed at baseline, 2 weeks, 4 weeks, and 6 weeks postintervention (see Fig. 1). All participants will be requested to complete follow-up assessments, except for those who will withdraw or will be withdrawn from the study. Those subjects will be asked to identify reasons for withdrawal. The assessment will last approximately 1 hour, with regular breaks provided to mitigate fatigue and burden.

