#### Secondary outcome measures

2.6.2

Active and passive range of motion of the kneeRoot mean square of surface EMG (measured bilateral rectus femoris, vastus medialis, and vastus lateralis)Knee function or deficiency using questionnaire (International Knee Documentation Committee score,^[21]^ Lysholm score,^[22,23]^ Knee outcome survey activities of daily living^[24]^)Quality of life (European Quality of Life-5 Dimensions 3-Level version^[25]^)Pain evaluation (visual analog scale)Satisfaction evaluation (5-point Likert scale)Frequency and duration for exercise using data from device or exercise logbook

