### Criteria for discontinuation

2.8

(1)Voluntary withdrawal of consent from the trial.(2)Aggravation of underlying disease.(3)Incompliance to intervention procedures (in this instance a specific reason must be recorded by the investigator).(4)Participation in the study is thought to interfere with other medical procedures.

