## Discussion

3

This study aims to investigate the feasibility and efficacy of a 6-week, structured home-based rehabilitation program for patients after ACL reconstruction using smart wearable device, which is an all-in-one home-based rehabilitation platform (range of motion exercise, strengthening using EMG biofeedback, electrical stimulation). This study is a prospective, single-center, randomized, controlled study. Subjects will be randomly allocated to 1 of 2 groups, the intervention (n = 20) or control group (n = 20). The following outcomes will be assessed at baseline, 2 weeks, and 6 weeks post the 6-week intervention program: quadriceps strength of the affect side as measured by a dynamometer (primary outcome); range of motion; root mean square of quadriceps muscle using surface EMG; knee function and subject's satisfaction score using questionnaire; quality of life; frequency and duration of exercise; and knee pain. It is hypothesized that patients receiving this rehabilitation program with device will show superior improvement in quadriceps muscle strength.

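### Feasibility is a stated aim, but participants who stop therapy leave the study, are not followed up and are counted in no listed outcome

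*Protocol article*

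**What the plan says.** **Aim.** The Discussion (section 3) states: "This study aims to investigate the feasibility and efficacy of a 6-week, structured home-based rehabilitation program". The abstract says the same.

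**Stopping.** Section 2.5.2 says of stimulation: "The stimulus intensity will be increased further to maximum subject tolerance". Section 2.7 allows for discomfort and notes that participants can control the intensity. If therapy has to end for discomfort or for another medical or subjective reason, "they will be withdrawn from the study immediately and reasons for discontinuation will be recorded". In context the therapy is the electrical stimulation, so ending it ends participation in the study. Section 2.8 lists four criteria for discontinuation. Discomfort is not named among them; the third is "Incompliance to intervention procedures (in this instance a specific reason must be recorded by the investigator".

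**Follow-up.** Section 2.6: "All participants will be requested to complete follow-up assessments, except for those who will withdraw or will be withdrawn from the study". It continues: "Those subjects will be asked to identify reasons for withdrawal".

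**Outcomes.** Sections 2.6.1 and 2.6.2 list no discontinuation, retention or tolerability outcome. The items closest to feasibility end the secondary list (two entries run together in the text): "Satisfaction evaluation (5-point Likert scale)Frequency and duration for exercise using data from device or exercise logbook". The abstract commits to intention-to-treat for the primary outcome only.

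**The concern.** Whether patients can keep using the device at home is at the centre of a feasibility question. Under the stated rules, a participant for whom stimulation proves intolerable, or who does not comply, can be taken out of the study and is then asked for a reason but for no further assessment. Satisfaction and exercise amount at the later visits are then measured in a group partly selected for having found the programme workable.

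The reasons for stopping are recorded, but no outcome turns them into a rate over those randomised. The trial could report good satisfaction and good exercise time among those who stayed without its listed outcomes showing how many did not. The likely direction is a feasibility conclusion that is too favourable.

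Withdrawal of consent and non-compliance can act in either arm. Section 2.5.3 gives the control group no electrical stimulation, so intolerance of stimulation is an additional route in the device arm alone.

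**Working it through.** **1. The plan's own figures (section 2.10.1).** Inputs: difference 33, SD 30, two-sided 5% level, 80% power, 30% attrition.

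- Normal approximation: n = 2 × (1.960 + 0.842)² × (30/33)² = 12.97, so 13 per group.
- t-test version: n = 14.002; power at 14 per group is 79.99%. This matches the stated 14.
- Attrition: 14 / (1 − 0.30) = 20 per group, as stated.

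The sample size reproduces and is not affected by this point. The plan thus allows for 20 − 14 = 6 participants per group to be lost.

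**2. The rules in sequence.**

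| Step | Section | Effect |
|---|---|---|
| Feasibility is an aim | Abstract; 3 | Continued use matters to the conclusion |
| Therapy ends for discomfort or other reasons | 2.7 | Participant leaves the study |
| Non-compliance | 2.8, item 3 | Ground for discontinuation, either arm |
| Withdrawn participants | 2.6 | No follow-up requested; reason asked |
| Outcome list | 2.6.1, 2.6.2 | No count of discontinuations |

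**3. What a stop rate would look like.** The counts are hypothetical, over 20 randomised to the device, with exact 95% CIs:

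- 2/20 = 10% (1.2% to 31.7%)
- 4/20 = 20% (5.7% to 43.7%)
- 6/20 = 30% (11.9% to 54.3%)

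**4. Effect on exercise amount.** Assumptions, none from the document: everyone uses the device 60 min/day while on it, and stoppers quit at the end of week 2. A stopper's six-week average is 60 × 2/6 = 20 min/day. The completer mean is 60. The mean over all randomised, with device use zero after stopping, is:

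- 2 stop: (18 × 60 + 2 × 20)/20 = 56 min/day; 60/56 = 1.07
- 4 stop: (16 × 60 + 4 × 20)/20 = 52 min/day; 60/52 = 1.15
- 6 stop: (14 × 60 + 6 × 20)/20 = 48 min/day; 60/48 = 1.25

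If the 6 stopped at week 4 instead, each would average 60 × 4/6 = 40, giving (840 + 240)/20 = 54 min/day; 60/54 = 1.11.

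**5. Effect on satisfaction.** Assume a completer mean of 4.2 on the 5-point scale and 6 leavers scoring between 1 and 3. Over all 20:

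- leavers at 1: (14 × 4.2 + 6 × 1)/20 = 3.24
- leavers at 3: (14 × 4.2 + 6 × 3)/20 = 3.84

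**The case against.** The strongest reply is that the data are less incomplete than the withdrawal rule suggests. Sections 2.5.1 and 2.5.2 say that exercise data are stored on the device automatically and will be used for analysis, and nothing excludes a stopper's log up to the day of stopping. Section 2.6 places assessments at 2, 4 and 6 weeks, so a late leaver may have earlier scores. Reasons are recorded under sections 2.6, 2.7 and 2.8, and the monitoring committee sees collected data every 3 months. Nor does the article say that exercise time will be averaged over completers; the analysis population for secondary outcomes is commonly left to a fuller document.

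Much of this stands, and it rules out several stronger readings that a reader might infer:

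- *That feasibility data exist only for completers.* Logs and visits before stopping may exist. How much the visits help is uncertain, because section 2.6 includes week 4 while the abstract, the Figure 1 legend and section 2.11 give only weeks 2 and 6 after baseline.
- *That section 2.8 has no place for device intolerance.* Such a stop could be filed under withdrawal of consent or under non-compliance with a specific reason. The weakness is that stops of one kind may be spread over several categories.
- *That only the device arm is affected.* The criteria in section 2.8 apply to both arms, and 30% attrition is assumed in each. Only stimulation intolerance is specific to the device.
- *That 30% of the device arm is expected to stop.* The 30% is attrition from any cause, and control over the intensity may keep stops for discomfort fewer.
- *That feasibility carries as much weight as efficacy.* The primary outcome, the sample size and the stated hypothesis all concern strength.

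What the reply does not remove is the stated combination of withdrawing the participant and requesting no further assessment. That is a written rule, not detail left to another document. Nothing stated commits the trial to counting stops over all randomised or to asking about satisfaction on exit.

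**Conclusion.** The point holds as a limitation of how the feasibility aim is measured. By the stated rules, later satisfaction and exercise data, in particular at week 6, would come mainly from participants who stayed, and discontinuation is not an outcome. The size cannot be fixed from the document. With 2 to 6 of 20 stopping at week 2 and equal use until then, completer-based device use would exceed all-randomised use by 7% to 25%. The stop rate itself would carry a wide interval, 12% to 54% for 6 of 20. These figures rest on assumed counts, use and stopping times, and on averaging over completers, which the article does not prescribe. They show scale and are not predictions. The efficacy sample size is untouched. The change is worth making because a stated aim depends on it and the cost is small.

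**What to change.** 1. Name a descriptive feasibility outcome: the proportion of all participants randomised to the device who stop stimulation or the device before week 6, by recorded reason, with a 95% CI.
2. Compute exercise amount over the full 6 weeks for all randomised participants, with device use set to zero after stopping. Keep device use apart from total exercise, since someone who stops the device may go on exercising without it.
3. Collect the satisfaction questionnaire when a participant stops.
4. Reconcile sections 2.6, 2.7 and 2.8 on the reasons for discontinuation and on whether stopping therapy also ends data collection. When therapy should stop is a clinical matter and is not addressed here.

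Cost: a short exit questionnaire, one extra table and some rewording. Reasons for stopping and device logs are already to be recorded. The downside is that the feasibility figures will probably look less favourable.

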### Criteria for discontinuation

2.8

(1)Voluntary withdrawal of consent from the trial.(2)Aggravation of underlying disease.(3)Incompliance to intervention procedures (in this instance a specific reason must be recorded by the investigator).(4)Participation in the study is thought to interfere with other medical procedures.

### Data and safety monitoring plan

2.9

A data and safety monitoring plan is established. Adverse events and data on the subjects’ assessments will be monitored. Data will be accessible only by the study team. Any hardcopy documentation will be stored in locked cabinets in locked offices. Data and safety monitoring committee (DSMC) guided by a prepared charter of roles and responsibilities. The DSMC will meet every 3 months to review recruitment, collected study data, and adverse events and will guide the study team regarding any needed action. Unanticipated events, adverse effects of the study subjects, and cases of noncompliance with the research protocol are reported to the IRB within a specified period. Major noncompliance, adverse events, and unintended events will be reported within 15 days. Minor noncompliance will be reported every 3 months.

### Statistical issues

2.10

#### Sample size calculation

2.10.1

This study was designed as an exploratory trial with 2 groups – intervention and control groups – using a dynamometer. The sample size calculation was based on the difference in the quadriceps strength (torque, Nm) between the 2 groups from the baseline to the 6-week follow-up. The following formula was used to calculate the number of participants needed in each group:
 
[figure not shown]

According to a previous study, the difference in the means of 6-week quadriceps strength was 33, with a standard deviation of 30.^[27]^ Based on the 5% 2-sided significance level and 80% power, at least 14 participants are needed in each group. With an attrition rate of 30%, our study will recruit a total of 20 participants in each group.

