**Methods and analysis::**

This is a protocol proposal for a prospective, single-center, randomized, controlled study. We plan to recruit adults discharged after ACL reconstruction; the recruited subjects will be randomly allocated to 1 of 2 groups, using a computer-generated randomization method: the intervention (n = 20) or control group (n = 20). The intervention group will receive a 6-week home-based rehabilitation program using smart wearable device. The control group will undergo a 6-week self-exercise program as normal. The following outcomes will be assessed at baseline, 2 weeks, and 6 weeks post the 6-week intervention program: quadriceps strength of the affect side as measured by a dynamometer (primary outcome); range of motion; root mean square of quadriceps muscle using surface electromyography; knee function using questionnaire; quality of life; subject's satisfaction score using questionnaire; frequency and duration of exercise; and knee pain. An intention-to-treat analysis will be conducted for the primary outcome.

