## Introduction

1

Injuries and surgical interventions of the knee often lead to weakness, pain, and reduced function of the quadriceps muscle.^[1,2]^ Rehabilitation to restore the range of motion and strength of the quadriceps muscle is essential for better postoperative outcomes.^[3,4]^ However, according to a previous study, only 35% to 76% of patients comply with the exercise regimens as prescribed.^[5]^ Reasons for such a low compliance may include physical and personal problems and, more importantly, lack of patient motivation.^[6,7]^ In addition, repetitive rehabilitation exercises may be boring, and routine outpatient care may be too burdensome on patients, requiring great effort and increased cost. Moreover, lack of professional facilities and/or manpower may also contribute to the problem of low compliance. These problems collectively can ultimately result in reduced compliance and thus increase the overall rehabilitation period and reduce the effectiveness of rehabilitation treatment.^[8,9]^

To improve the overall treatment outcomes, new rehabilitation techniques that focus primarily on improving patient motivation, and thereby compliance, may be necessary. To such effort, various medical devices and rehabilitation programs have been developed, manufactured, and researched. Approaches that incorporate games or gaming techniques derived from the video game industry have been presented as inexpensive and promising alternatives to regular physical therapy or home-based rehabilitation exercises.^[10]^ In recent years, much attention has been focused on combining games and wearable technology into exercise programs, allowing patients to have more fun and an immersive experience while getting the benefits of exercise. By removing the sense of obligation by associating exercise with fun, this combination of game and wearable technology with exercise has the ability to improve patient compliance while reducing the aforementioned burden of treatment.^[11]^ Furthermore, data acquired from various sensing system in wearable devices and game scoring systems can provide more objective monitoring, which could be used to provide better feedback.^[12,13,14]^

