### Randomization and blinding

2.4

Participants in this trial will be randomly assigned in a ratio of 1:1 to either the control group (home-based self-exercise program) or the intervention group (home-based exercise program using device). Participants will be allocated to 1 of the 2 groups via blocked randomization with variable size blocks to ensure an equal number of participants in both groups. This method reduces selection bias, especially in studies with small sample sizes.^[20]^ Allocation will be concealed using sequentially numbered opaque envelopes. These envelopes are stored in a lock-sealed location. A researcher without direct contact with patients will select and open the envelope in the presence of a physiotherapist to see the assignment number. This randomized assignment number will then be recorded in the case record form, and the study will be performed according to the assigned group. Due to the characteristics of this test method, the outcome assessor will also be blinded to group allocation. Once the intervention is completed, the researcher responsible for the statistical analysis will receive an Excel spreadsheet with the necessary data without any identifiable parameters. A flow diagram of the study is shown in Figure 2.

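### The 30% attrition allowance has no slack and is not reconciled with rules that let non-compliant participants leave without a primary outcome assessment

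*Protocol article*

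**What the plan says.** The Protocol article, section 2.10.1 (Sample size calculation), takes its inputs from a previous study: "the difference in the means of 6-week quadriceps strength was 33, with a standard deviation of 30". It continues: "Based on the 5% 2-sided significance level and 80% power, at least 14 participants are needed in each group". The allowance for loss follows: "With an attrition rate of 30%, our study will recruit a total of 20 participants in each group". No source is given for the 30%, and the section does not say which kinds of loss it covers.

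Three other places decide who will have a primary outcome:

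- Section 2.8 (Criteria for discontinuation) lists, as its third criterion, "Incompliance to intervention procedures (in this instance a specific reason must be recorded by the investigator". It sets no threshold.
- Section 2.6 (Assessment): "All participants will be requested to complete follow-up assessments, except for those who will withdraw or will be withdrawn from the study".
- The abstract, under Methods and analysis: "An intention-to-treat analysis will be conducted for the primary outcome".

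The Introduction motivates the trial by poor adherence. It reports from a previous study that "only 35% to 76% of patients comply with the exercise regimens as prescribed", and it hypothesises that the device programme will improve compliance.

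**The concern.** The protocol builds its case on poor compliance, makes non-compliance a reason to leave the trial, and does not ask those who leave to attend the assessment on which the primary analysis depends. The loss allowance is a single unexplained figure that leaves exactly the required number.

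Two things are at stake. The first is power: every loss beyond six per arm takes the comparison below the stated 80%, and a null result could then be credited with more power than it had. The second is the intention-to-treat comparison: a participant removed for non-compliance and never measured cannot contribute an observed six-week outcome, whatever the analysis is called. Because compliance is something the device is meant to change, such removals may also differ between arms.

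**Working it through.** **Inputs.** Difference 33, SD 30, two-sided 5%, 80% power, 14 needed, 20 recruited and 30% attrition per group all come from section 2.10.1. Section 2.4 gives equal allocation: "Participants in this trial will be randomly assigned in a ratio of 1:1". I take the effect inputs at face value.

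**Step 1: reproduce the 14.** The standard formula for two means is n = 2(z₀.₉₇₅ + z₀.₈₀)²σ²/δ² per group.

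2 × (1.960 + 0.8416)² × 30²/33² = 2 × 7.849 × 0.8264 = 12.97, so 13 by the normal approximation.

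With the noncentral t distribution, the noncentrality is δ/(σ√(1/n₁ + 1/n₂)). At 14 per group this is 1.1 × √7 = 2.91 on 26 degrees of freedom, and power is 79.99%. The stated 14 is therefore the t-test answer, and it is correct.

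**Step 2: reproduce the 20.** 14/(1 − 0.30) = 20, and 20 × 0.70 = 14. This is also correct. It tolerates six losses per arm and no more.

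**Step 3: power if loss differs from 30%.** Same inputs, two-sample t-test, 20 recruited per arm:

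| Assessed per arm | Loss | Power |
|---|---|---|
| 15 | 25% | 83% |
| 14 | 30% | 80% |
| 13 | 35% | 77% |
| 12 | 40% | 73% |
| 11 | 45% | 69% |
| 10 | 50% | 64% |

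A shortfall in one arm is enough to lower power. As an extreme illustration, 14 against 7 gives a noncentrality of 1.1/√(1/14 + 1/7) = 2.38 on 19 degrees of freedom and power of 62%.

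**Step 4: set the rules side by side.**

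1. Section 2.8 allows discontinuation for non-compliance.
2. Section 2.6 does not ask withdrawn participants to attend follow-up. Section 2.7 (Harms and benefits) goes the same way: a participant whose therapy has to be terminated for discomfort or other reasons is withdrawn from the study. Stopping the intervention and leaving the study are thus treated as one event.
3. The abstract promises intention-to-treat for the primary outcome. Those who leave under (1) and (2) can be in that analysis only through data that were not collected.
4. Section 2.10.1 does not say whether the 30% includes them.

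**Step 5: balance between arms.** The Introduction's hypothesis implies more non-compliance among controls. Withdrawal for discomfort from electrical stimulation can arise only in the device arm, because section 2.5.3 says controls receive none. Unequal loss is therefore plausible, but the documents do not settle its direction.

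**The case against.** The stronger reading that a reader might infer is that the 30% contradicts the protocol's own compliance figure. If 35% to 76% comply, then 24% to 65% do not; remove them all and 20 × 0.35 = 7 to 20 × 0.76 = 15.2 per arm remain, so the promised 14 is not delivered. The documents do not support this, for four reasons.

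- 30% lies inside 24% to 65%. At 24% loss about 15 remain and power is about 83%. There is no contradiction and no arithmetic error.
- The compliance figure is background from a previous study about following exercise regimens as prescribed. It is not offered as a retention forecast for this trial, and it is not tied to home exercise like that of the control arm.
- Imperfect adherence is not removal. The discontinuation criterion has no threshold and requires a specific recorded reason, which suggests case-by-case decisions. Section 2.5 has exercise status checked at 2, 4 and 6 weeks, with encouragement to continue. Section 2.6.2 makes exercise frequency and duration a secondary outcome, which would serve little purpose if everyone who under-exercised were removed.
- Treating the published range as a probability distribution, so as to say that most of it exceeds 30%, has no basis.

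The trial is also described as exploratory, which softens the consequence of a power shortfall.

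All of this stands against the stronger reading. It does not answer the narrower point. Intention-to-treat keeps a non-compliant participant in the comparison only if that participant is measured, and sections 2.6 and 2.8 together allow otherwise. The 30% has no stated scope, and the calculation has no margin to absorb the uncertainty.

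**Conclusion.** The point holds in a limited, conditional form. The sample size arithmetic is correct. What is unresolved is how the 30% allowance, the discontinuation criterion, the exemption from follow-up and the intention-to-treat promise fit together. As written, they let non-compliance become missing primary data that the allowance may or may not cover, possibly to different degrees in the two arms.

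The size depends on how the criterion is applied, which the protocol does not say. Power stays at 80% or above while at least 14 per arm are assessed, and is 77% at 13 and 64% at 10. These values assume the protocol's difference and SD, a two-sample t-test on assessed participants, and equal loss in both arms. They are a sensitivity range, not a forecast, and 7 to 15 per arm should not be read as the expected number. The matter should be corrected because the remedy is cheap and protects both the stated power and the randomised comparison.

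**What to change.** Reconcile the abstract's intention-to-treat statement with sections 2.6, 2.8 and 2.10.1, and bring the withdrawal wording in 2.7 into line. The following concerns outcome collection and analysis only; when the intervention itself is stopped remains a clinical matter for the trial team.

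- In 2.6 and 2.8, separate stopping the intervention from leaving the study. State that participants who do not comply with or stop the intervention are still asked to attend the six-week assessment and are analysed in the group to which they were randomised, unless they withdraw consent.
- In 2.10.1, state that the 30% covers only consent withdrawal and loss to follow-up.
- If non-compliant participants will nevertheless leave without assessment, say in 2.10.1 that the 80% power is conditional on at least 14 assessed per arm. Show power at higher loss as a sensitivity range, such as the table above, without presenting any of those numbers as expected.

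The cost is a few sentences and a little more effort to obtain six-week data from people who have stopped exercising. Enrolment and the visit schedule need not change.
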